**Assessment of weaning from cardiorespiratory support**

- Successful weaning is defined as no requirement for ventilatory support after extubation (mechanical support) or support from ECMO for 48 hours. The primary objective will be measured as percentage of patients successfully weaned after 30 days of follow-up. The percentage of patients weaned at 20 days post-intubation will be a relevant secondary endpoint.

The ***secondary objectives*** of the study are:

1. **Assessment of hemodynamic status**

Hemodynamic status will be assessed by continuous blood pressure measurements (systolic, diastolic and mean BP) and the use of inotropic and vasoactive drugs.

1. **Assessment of pulmonary function**

Pulmonary function will be assessed by arterial measurement of blood gases, Horowitz-Index (pO2/FiO2) and lactate.

1. **Assessment of hepatic and renal function**

Hepatic and renal function will be assessed by laboratory measurements in blood and urine volume

1. **Assessment of cardiac function**

Echocardiographic assessment of systolic and diastolic function will be performed. Measurements of cardiac troponin-I will be used to assess myocardial injury

1. **Assessment of the course of** *COVID-19* **infection**

COVID-19infection will be assessed by inflammatory indices and their course (daily changes and absolute values) in blood (IL6, Procalcitonin, D-Dimers, Ferritin and CRP), temperature monitoring and time needed for the patient to become negative in COVID-19.

1. **Assessment of clinical outcome and safety**

Major events (*death, cardiac Arrest, electromechanical dissociation, pulmonary embolism, new myocardial infarction, stroke, pulmonary edema, cardiogenic shock and hypotension, septic shock, pulmonary embolism, serious bleeding*) and minor (*myocarditis, Venous Thromboembolism, left Ventricular mural thrombus, renal failure, hepatic failure, stress ulcers, minor bleeding,* [*paroxysmal supraventricular tachycardia*](http://emedicine.medscape.com/article/156670-overview)*and*[*atrial fibrillation*](http://emedicine.medscape.com/article/151066-overview)*, rythm disturbances*) will be recorded during the follow up period.

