## 5.5 Recording and evaluation of clinical safety criteria

The following safety clinical criteria will be evaluated:

- Death
- Sudden cardiac death
- Cardiac Arrest
- Electromechanical dissociation
- Pulmonary Embolism
- Venous Thromboembolism
- Myocarditis
- Left Ventricular mural thrombus and/or embolism
- Congestive heart failure
- Cardiogenic shock and hypotension
- Septic shock
- New myocardial infarction
- Stroke
- Renal Failure
- Hepatic Failure
- Stress Ulcers
- Bleeding
- Thrombocytopenia
- Disseminated intravascular coagulation
- Ventricular fibrillation or Sustained ventricular tachycardia
- Rythm disturbances and serious bradycardia that require a pacemaker implantation
- [Paroxysmal supraventricular tachycardia](http://emedicine.medscape.com/article/156670-overview), [atrial flutter](http://emedicine.medscape.com/article/151210-overview), and [atrial fibrillation](http://emedicine.medscape.com/article/151066-overview)
- Vital signs (heart rate, blood pressure)

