## 5.7 Recording and evaluation of laboratory and instrumental safety criteria

A number of laboratory measurements will be performed in blood samples in order to evaluate disturbances in blood cells, renal dysfunction, hepatic dysfunction and dysfunction in glucose homeostasis.

The following parameters will be measured Haemoglobin, white blood cells, platelets, urea, creatinine, Glucose, CPK, LDH, AST, ALT, γ-GT, Total and Direct bilirubin, Albumin and total protein, INR, fibrinogen, d-dimer, Electrolytes (Na, K, Ca, phosphate, Mg), Troponin I, BNP, urine volume.

12-leads ECG will be performed every day during ICU stay and every 2 days during hospital stay to assess basal heart rate and cardiac rhythm.

Pulmonary function will be assessed by regular measurements of blood gases (pO2, pCO2, blood pH,lactate).

The course of *COVID-19* infection will be assessed by regular temperature monitoring, inflammatory indices (white blood cells, CRP, IL6, Procalcitonin, Ferritin, D-Dimers) and positivity for active replication of *COVID-19.*

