## Thus, in ThySupport, the dose administered will be 0.8μg/kg i.v. bolus, starting within 60min after respiratory support and will be followed by an infusion of 0.113μg/kg/h i.v. for 48 hours (therapeutic dose). After the first 48h, a maintenance dose will be administered corresponding to 50% of the therapeutic dose (0.057 μg/kg/h i.v.). Drug administration will stop after successful weaning or end of followup (maximum 30 days).

***Figure 8.*** *Schematic of drug administration schedule inThySupport study*

In previous studies in CABG patients it was shown that administration of the dose of T3 proposed here (0.8μg/kg at the end of ischaemia followed by an infusion of 0.113μg/kg/h) resulted in short-term supranormal serum T3 levels without any effects on heart rate or arrhythmias or any other adverse event reported.

[figure not shown]

***Figure 9.*** *Pharmacokinetics of T3 in CABG patients*

More importantly, data from the ThyRepair study (EudraCT: 2016-000631-40) conducted in patients with ST-elevation myocardial infarction showed that administration of the drug under investigation at the proposed doses (0.8μg/kg i.v. bolus followed by an infusion of 0.113μg/kg/h i.v. for 48 hours) resulted in significant increase in the levels of T3 above normal that lasted for 72 hours without any significant adverse event.

[figure not shown]

***Figure 10****: Levels of triiodothyronine in serum during hospitalization in patients after acute myocardial infarction treated with placebo and T3*

Administration of high dose T3 resulted in a non-significant increase in heart rate during the first 3 days (Figure 11).

***Figure 11****: Heart rate assessed during hospitalization in STEMI patients treated with placebo and T3*

***Table.*** *Adverse events during hospitalization in Thy-Repair trial (interim analysis).*

| **Adverse Events** | **placebo Group**  **(n=17)** | **T3 Group**  **(n=16)** |  |
| --- | --- | --- | --- |
| Atrial Fibrillation | 7.7% | 19% | *p=0.25* |
| Thrombus in Left Ventricle | 12% | 12.5% | *p=0.94* |
| Pericardial Effusion | 6% | 6.25% | *p=0.9* |
| Minor Hemorrhages | 12% | 19% | *p=0.57* |
| Diuretics Use during first 24 hours | 40% | 50% | *p=0.7* |
| Need for Sympathomimetics administration after PPCI | 30% | 19% | *p=0.45* |
| Transient Fever wave>37.8 | 0% | 31% | *p=0.01* |

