## The increased temperature that was observed in some patients in ThyRepair study involved a single fever wave up to 38.5 during the second day of treatment that receded after paracetamol administration. This wave was recorded in 1 to 3 patients receiving T3. It didn’t cause any diagnostic issues since other inflammatory indices did not increase.

Thyroid hormones are eliminated 70-80% by the kidneys. In ThyRepair study we enrolled patients with GFR more than 60 ml/min and no problem was recorded after T3 administration. A reduction of GFR<30ml/min could increase T3 levels in blood. However, this increase is blunted by attenuation of the conversion of T4 to T3 which is reported under conditions of acute or chronic renal failure (37). It should be noted that the therapeutic index of T3 is high. In case there is a potential adverse event that could be linked to T3 in a patient with severe renal failure, urgent unblinding of the patient can be performed and the levels of T3 can be determined.

The liver has a secondary role in the elimination of thyroid hormones by 25%. Acute or chronic hepatic injury reduces the conversion of T4 to T3. Thus, in patients with hepatic injury, normal or increased levels of T4 and low levels of T3 have been reported. (Kano T, et al.. Serum thyroid hormone levels in patients with fulminant hepatitis: usefulness of rT3 and the rT3/T3 ratio as prognostic indices (38). Based on the above, administration of T3 in patients with hepatic injury will not result in higher than expected levels of T3 in blood.

Further analysis of preliminary data from ThyRepair show that although infarct size was similar between the placebo and T3 group, an improvement of LV ejection fraction is evident in T3 treated STEMI patients early and late after the index event (Figure 12 and 13).

***Figure 12.*** *CMR analysis shows no difference in infarct size (extent of injury) between placebo and T3 group.*

[figure not shown]

***Figure 13.*** *Left ventricular ejection fraction assessed by echocardiography at different time points in STEMI patients treated with placebo and T3.*

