## Expected adverse drug reactions

All expected adverse drug reactions and all expected serious adverse events are listed below ***otherwise they will be reported as SUSARs***.

There are possible side-effects associated with triiodothyronine that can affect individuals in different ways. Serious side effects are rare and include an allergic reaction, chest pain, shortness of breath and arrhythmias. In the treatment of myxedema, side effects associated with the use of intravenous T3 have included arrhythmias (5% of patients) and tachycardia (3%). Hypotension and myocardial infarction occurred in approximately 1.5% of hypothyroid patients that received T3. Angina and congestive heart failure occurred in approximately fewer than 1% of patients.

Other, less serious side effects consist of:

- insomnia;
- headache;
- leg cramps;
- diarrhea, abdominal cramps
- seizures, tremors, nervousness, or irritability;
- menstrual irregularities.
- phlebitis
- Nausea or vomiting
- fever, sweating, or heat intolerance;
- changes in appetite, or weight loss;
- Hypertension
- Skin flushing
- Hypoglycemia
- Adrenal insufficiency

Sometimes, unexpected adverse drug reactions and unexpected serious adverse events become ‘expected’ during the trial, in which case the protocol should be amended and such events would not need reporting. The Chief Investigator and Data Monitoring Committee, will determine whether any events become ‘expected’ during the course of the trial and apply for approval for a substantial amendment.

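### Temperature is an index of COVID-19 course although the protocol's own data link the same initial T3 dose to fever, and section 5.5 does not name fever as a safety criterion

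*Protocol*

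**What the plan says.** Protocol section 3, under the secondary objective on the course of COVID-19 infection, lists blood inflammatory indices together with "temperature monitoring and time needed for the patient to become negative in COVID-19". Section 5.7 gives temperature the same role: the course of the "infection will be assessed by regular temperature monitoring, inflammatory indices" and positivity for active viral replication.

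The clinical safety list in section 5.5 ends with "Vital signs (heart rate, blood pressure") and has no temperature or fever item. The major and minor events in section 3 do not include fever either.

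Section 9 (Dosage and Safety) states that the dose for the first 48 hours is identical to the ThyRepair dose. The ThyRepair interim table there, with 17 placebo and 16 T3 patients, has the row "Transient Fever wave>37.8 | 0% | 31% | *p=0.01". The text above the table says that this regimen "resulted in significant increase in the levels of T3 above normal that lasted for 72 hours without any significant adverse event". The text after it describes one fever wave on the second day and adds: "This wave was recorded in 1 to 3 patients receiving T3". It then says the fever caused no diagnostic difficulty because other inflammatory markers did not rise.

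Section 12 lists "fever, sweating, or heat intolerance" among the expected, less serious reactions to T3.

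**The concern.** An index of infection course should differ between arms only through the infection. Here the protocol's own data suggest that the study drug moves one of the chosen indices directly. If T3 patients run warmer, the comparison cannot separate slower resolution of infection from a pharmacological effect. The distortion would make T3 look worse on this objective.

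The reason the protocol gives for not worrying does not carry over. In ThyRepair the patients had myocardial infarction, so unraised inflammatory markers could show that a fever was not infectious. In ThySupport the patients have severe COVID-19, and the same kinds of marker are followed because they are expected to reflect the disease. Exposure is also longer: up to 30 days, with a maintenance infusion after the first 48 hours, against 48 hours in ThyRepair.

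Two lesser matters go with this. The one row of the ThyRepair table with p below 0.05 has no counterpart in the section 5.5 list. And the text beside the table gives a count that, as printed, is smaller than the table's.

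**Working it through.** **Inputs** (Protocol, section 9, ThyRepair interim table): T3 n=16, fever 31%; placebo n=17, fever 0%; printed p=0.01.

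**Step 1: recover the counts.** 0.31 × 16 = 4.96, so 5 patients (5/16 = 31.25%). Placebo is 0/17.

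**Step 2: reproduce the printed p value.** Pearson chi-square without continuity correction, with a=5, b=11, c=0, d=17:

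N(ad − bc)² / [(a+b)(c+d)(a+c)(b+d)] = 33 × (5×17 − 11×0)² / (16 × 17 × 5 × 28) = 238,425 / 38,080 = 6.26, which gives p = 0.012. This rounds to the printed 0.01.

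Other tests of the same table give Fisher exact 0.018, Barnard 0.022 and Yates-corrected chi-square 0.044. All are below 0.05. None is below 0.05/7 = 0.0071, the Bonferroni threshold for the seven rows of the table.

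**Step 3: precision.** Exact 95% interval for the T3 rate: 11% to 59%. For the placebo rate: 0% to 20%. Difference 31 percentage points, Newcombe 95% interval about 6 to 56.

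**Step 4: compare the text's count with the table.** Each possible T3 count is set against 0/17:

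| Febrile T3 patients | Rate | Chi-square p |
|---|---|---|
| 1/16 | 6% | 0.30 |
| 2/16 | 12.5% | 0.13 |
| 3/16 | 19% | 0.06 |
| 5/16 | 31% | 0.01 |

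Only 5 of 16 yields both the printed percentage and the printed p value. The table agrees with itself, and the sentence with 1 to 3 patients does not agree with it.

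**Step 5: possible size in this trial.** This assumes that the ThyRepair rate carries over to 30 T3 patients, which the protocol does not establish: 0.3125 × 30 = 9.4, about 9 patients. Over the interval, 0.110 × 30 = 3.3 to 0.587 × 30 = 17.6, about 3 to 18. No figure is available for the maintenance phase.

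**Step 6: where temperature and fever appear.**
- As an infection index: section 3 and section 5.7.
- As a named clinical safety criterion: not in section 5.5, nor in the section 3 event lists.
- Elsewhere on the safety side: fever is an expected reaction (section 12), hyperthermia is in the toxicity procedures, temperature is recorded every 24 hours in ICU alongside adverse event evaluation (section 11), and individual adverse events are collected to day 30 (section 5.6).

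**The case against.** The strongest reply is that fever is already covered. Temperature is recorded daily, adverse events of any kind are collected for 30 days, fever is a listed expected reaction, and section 5.7, which contains the temperature monitoring, is headed as safety criteria. This stands. A reader might infer that fever escapes safety monitoring altogether, or that the signal is concealed inside an efficacy measure. The documents do not support that: the row is printed with its p value and the fever has its own paragraph. What remains is narrower. Section 5.7 gives temperature only the infection role, and section 5.5 does not name it.

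A second reply is that the effect on conclusions is small. Temperature is one of several indices under one of six secondary objectives, no threshold or test is fixed for it, and ThyRepair described a single wave that subsided. The blood indices are followed for daily change as well as level, so raised starting values do not by themselves prevent seeing whether they move with a fever. This too largely stands. It limits the size of the problem but does not make temperature a clean index.

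Third, the apparent contradictions may be matters of language. The count of 1 to 3 could be a slip for 1 in 3, which is 33% and close to the table's 31%. Significant, in the sentence on adverse events, can mean clinically important. Both readings are plausible, so an intention to understate the signal should not be inferred. As printed, however, the count is wrong against the table and the other sentence is ambiguous directly above a row with p=0.01.

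Finally, the fever data are interim, small and unadjusted for seven comparisons, and come from a different population. It would be too strong to say that the dose has been shown to cause fever, or that drug fever will be taken for infection. Association, and a risk of misreading, are what the data support.

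**Conclusion.** The point holds as a limited one. The protocol uses temperature to judge the course of COVID-19 while its own evidence associates the same first-48-hour T3 dose with fever (5/16 against 0/17, p=0.012; T3 rate 31%, 95% interval 11% to 59%) and it lists fever as expected. The temperature comparison may therefore mix drug effect with infection, and the bias would run against T3. If the rate carried over, about 9 of 30 T3 patients would be affected, with a range of about 3 to 18.

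This rests on two assumptions: that the small ThyRepair sample is informative about ventilated COVID-19 patients, and that temperature would be compared between arms as part of the secondary objective. The primary endpoint, successful weaning at 30 days, is not touched, and a bias in this direction would not produce a false claim of benefit.

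The missing section 5.5 entry and the mismatched patient count are defects of wording. The same table's placebo atrial fibrillation figure of 7.7% is not attainable with 17 patients (1/17 = 5.9%, 2/17 = 11.8%). A reader might take it as further evidence here, but it is a background error with no bearing on how temperature is used.

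**What to change.** 1. Section 5.5: add temperature/fever to the safety criteria, summarised by arm, and include it in the interim safety review described in section 14.
2. Sections 3 and 5.7: temperature may stay, but report it separately from the infection-course indices and state that T3 affects it. Deleting it altogether is not necessary.
3. Section 9: reconcile the 1 to 3 patients with the table's 5 of 16 against 0 of 17, after checking the source data. Say what is meant by no significant adverse event, given the fever row.

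Tabulation by dosing phase (first 48 hours, maintenance) would be useful, but that detail can sit in the statistical analysis plan.

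The cost is protocol wording only, since temperature is already recorded every 24 hours in ICU. The downside is a slightly less favourable safety statement and one fewer clean index of infection course. No change to dosing or clinical management is implied.

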**4. INCLUSION AND EXCLUSION CRITERIA**

In this prospective study all patients diagnosed with COVID19 pulmonary infection receiving endotracheal [mechanical ventilation](https://www.sciencedirect.com/topics/medicine-and-dentistry/artificial-respiration" \o "Learn more about Artificial Respiration from ScienceDirect's AI-generated Topic Pages) or ECMO will be considered for enrolment in the study. The study protocol will be approved by the institutional review board and all included patients or legal representatives will provide informed consent to participate in the study.Experimental and clinical data show that maximum efficacy of T3 is achieved when the drug is administered early under hypoxia or hypoxia/reoxygenation conditions where production free oxygen radicals is increased. Thus, the study aims to provide rapid initiation of treatment with T3 within 1 hour of intubation.

In accordance with Good Clinical Practice, all patients will be treated according to the existing guidelines for management of ARDS in patients in ICU requiring [mechanical ventilation](https://www.sciencedirect.com/topics/medicine-and-dentistry/artificial-respiration) or ECMO and patients with septic shock (14, 46, 47).

"Recent guidelines on mechanical ventilation in ARDS provide evidence-based recommendations related to 6 interventions, including low tidal volume and inspiratory pressure ventilation, prone positioning, high-frequency oscillatory ventilation, higher vs lower positive end-expiratory pressure, lung recruitment maneuvers, and extracorporeal membrane oxygenation" (46)

In order to avoid masking the favorable action of T3, we exclude patients that have already received corticosteroids or sympathomimetics which increase viral load and their administration has been associated with increased mortality in sepsis. However, if corticosteroids or sympathomimetics are considered necessary during ARDS treatment of ICU stay, they can be added after administration of the investigational drug has started.

**4.1 MAIN INCLUSION CRITERIA**

- *Patients diagnosed with pulmonary infection and/or ARDS (COVID-19) due to SARS-Cov2viral infection, admitted in ICU and require mechanical ventilation or ECMO*
- *Male and female with Age>18 years old*
- Consent to use an effective contraceptive method beginning from patient enrolment and during participation in the trial, if potential fertile women are enrolled
- *Signed informed consent*

Potential fertile women enrolled in the study will undergo a pregnancy test that will exclude any possibility of present pregnancy. As potential fertile woman is considered every woman who has a menstrual cycle and has not been subjected in surgical sterilization or is not in a post-menopausal condition. In the case of pregnancy, the patient will immediately and automatically be excluded from enrolment and all necessary assistance will be guaranteed for the mother and the child and the pregnancy will be followed until the delivery.

**4.2 MAIN EXCLUSION CRITERIA**

- *Pregnant or breast-feeding women*
- *Known hypersensitivity in the active substance or any of the excipients*
- *Severe systemic disease (e.g. cancer) before infection accompanied by reduced life expectancy <6 months*
- *Participation in another trial of an investigational drug or device*
- *Corticosteroid Use before initiation of treatment*
- *Sympathomimetic Use before initiation of treatment (epinephrine, norepinephrine, dobutamine, dopamine, phenylephrine)*

**5. Data Collection Procedures**

**5.1 Weaning from cardiorespiratory support**

Weaning from ventilatory support plus extubation (in non-tracheostomised patients) will be attempted, when clinically deemed feasible by the treating intensivist. Level of consciousness, muscle strength, ability to cough and protect airways, renal function and fluid balance will be assessed during an attempt to wean. Successful weaning will be defined as no requirement for ventilatory support for 48 hours after extubation, or (in tracheostomised patients) discontinuation of ventilatory support or no need for ECMO support for 48 hours.

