**3. OBJECTIVES**

The ***primary objective*** of the study is to determine whether the administration of intravenous T3 in ICU patients *diagnosed with pulmonary infection due to COVID-19* facilitates weaning from cardiorespiratory support compared to placebo.

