### Maximum duration of treatment of a subject

Each subject will be treated until successful weaning or end of follow up. The maximum treatment duration of a subject may reach 30 days.

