## Study assessments

***During stay in the ICU the following parameters will be recorded every 24 hours:*** Blood pressure, heart rate, oxygen saturation, temperature, blood gases, urine volume, need for inotropic support, standard medication, laboratory tests, ECG and evaluation of AEs.

**Echocardiographic analysis** will be performed every 48 hours during ICU stay

**Thyroid hormone levels** (Serum total T3, total T4 and TSH) will be determined at baseline and at 24h, 48h, 72h, and every 3 days till termination of drug administration or end of follow-up.

**Successful weaning** will be defined as no requirement for ventilatory support for 48 hours after extubation, or (in tracheostomised patients) discontinuation of ventilatory support or no need for ECMO support for 48 hours. The percentage of successfully weaned patients and the duration of required mechanical respiratory support or ECMO (in days) will be recorded.

**Individual adverse events** (AE) will be evaluated by the investigators and they will be reported to the sponsor. This includes the evaluation of seriousness, causality and expectedness and any relationship between the investigational medicinal product(s) and/or concomitant therapy and the adverse event. Adverse events will be recorded during 30 days follow-up. A 24h telephone line will be available for all patients in order to communicate with a study investigator and report any adverse event in the case of discharge from hospital.

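### Sections 5.1 and 11 list 48 hours off ECMO as its own route to successful weaning, so a patient still ventilated could be scored a success and have the study drug stopped

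*Protocol*

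**What the plan says.** Patients on either support are eligible: section 4.1 admits those "admitted in ICU and require mechanical ventilation or ECMO". The primary objective in section 3 is whether T3 "facilitates weaning from cardiorespiratory support compared to placebo".

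Successful weaning is defined in three places.

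- **Section 3** (Assessment of weaning from cardiorespiratory support): "no requirement for ventilatory support after extubation (mechanical support) or support from ECMO for 48 hours".
- **Section 5.1**: either 48 hours without ventilatory support after extubation, or, following a parenthesis that names tracheostomised patients, "discontinuation of ventilatory support or no need for ECMO support for 48 hours".
- **Section 11** (Study assessments): the same wording as section 5.1.

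Section 5.1 introduces its definition with "Weaning from ventilatory support plus extubation (in non-tracheostomised patients) will be attempted".

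The same term controls dosing. Section 9 says under Maximum duration of treatment: "Each subject will be treated until successful weaning or end of follow up". Under Dosage and Safety it says: "Drug administration will stop after successful weaning", or at the end of follow-up, with a maximum of 30 days.

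**The concern.** In sections 5.1 and 11 the ECMO clause has its own negation and follows its own 'or'. Grammatically it is sufficient alone, and nothing in the sentence requires the patient to be off the ventilator as well. Section 3 puts both supports under a single negation, which most naturally means that neither is needed. No section says which wording governs.

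Two things depend on this. The first is scoring: a patient off ECMO but still ventilated is a failure under section 3 and can be a success under sections 5.1 and 11. The second is treatment: the infusion stops at successful weaning. Stopping it in a ventilated patient would run against the reason section 9 gives for the maintenance dose, namely that prolonged respiratory support keeps T3 low. A statistical analysis plan could settle the scoring later, but it could not restore an infusion already stopped.

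**Working it through.** **Comparing the definitions.** The parenthesis in sections 5.1 and 11 can be read in two ways. On the narrow reading it covers only ventilator discontinuation. On the wide reading it also covers the ECMO clause.

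| Patient | Section 3 | 5.1/11, narrow | 5.1/11, wide |
|---|---|---|---|
| Extubated, free of both supports for 48 h | weaned | weaned | weaned |
| Off ECMO 48 h, still ventilated by tracheostomy | not weaned | weaned | weaned |
| Off ECMO 48 h, still ventilated by endotracheal tube | not weaned | weaned | not weaned |
| Ventilated by endotracheal tube, never on ECMO | not weaned | weaned | not weaned |

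The second row differs from section 3 on either reading. The third differs only on the narrow one. The last row cannot be intended, which suggests a slip in drafting and not a chosen rule.

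**The plan's power figure.** Section 6 gives 15% versus 50%, 30 per arm, two-sided alpha 0.05 and 84% power. With the pooled normal approximation:

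- mean rate = (0.15 + 0.50)/2 = 0.325
- SE under the null = √(2 × 0.325 × 0.675/30) = 0.1209
- SE under the alternative = √((0.15 × 0.85 + 0.50 × 0.50)/30) = 0.1122
- power = Φ((0.35 − 1.96 × 0.1209)/0.1122) = Φ(1.007) = 84.3%

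The stated figure reproduces.

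**What re-scoring would do.** One patient re-scored moves that arm's percentage by 1/30 = 3.3 points. To go further, a share r of failures re-scored as weaned must be assumed, here equal in both arms. The protocol gives no ECMO share from which to estimate r.

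- control rate = 0.15 + 0.85r
- T3 rate = 0.50 + 0.50r
- difference = 0.35(1 − r)

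| Assumed r | Rates | Difference | Expected re-scored (control / T3) | Pooled power |
|---|---|---|---|---|
| 0 | 15% vs 50% | 35.0 points | 0 / 0 | 84.3% |
| 5% | 19.3% vs 52.5% | 33.3 points | 1.3 / 0.8 | 78.0% |
| 10% | 23.5% vs 55% | 31.5 points | 2.6 / 1.5 | 71.5% |
| 20% | 32% vs 60% | 28.0 points | 5.1 / 3.0 | 58.9% |

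Expected failures are 30 × 0.85 = 25.5 in control and 30 × 0.50 = 15 on T3; the fourth column multiplies these by r. A re-scored patient must have been on ECMO, come off it for 48 hours and still not be free of the ventilator for 48 hours by day 30. So r cannot exceed the ECMO share among failures. On the wide reading only tracheostomised patients qualify, and r is smaller again.

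**A single result near plan.** 5/30 versus 15/30 gives chi-square p = 0.006. Re-scoring 3 of 25 control failures (12%) and 2 of 15 T3 failures (13%) gives 8/30 versus 17/30, p = 0.018 (Fisher p = 0.035). The conclusion survives.

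**The case against.** The strongest reply is that nobody would apply the literal text. It would make every intubated patient who never needed ECMO a success, which is absurd. The context also points to the stricter meaning: the stated objective is weaning from cardiorespiratory support, section 5.1 opens with ventilator weaning plus extubation and lists airway and muscle-strength checks, and the maintenance-dose rationale assumes continued infusion while the patient is ventilated. Section 3 also joins the two supports with 'or', so the three definitions might be read alike, each patient being judged on the support received.

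Much of this stands. The stricter meaning is very probably intended, and a flat contradiction between the sections would be too strong a charge. But judging by the support received still leaves open the patient who was on both and has come off only ECMO. A primary endpoint and a dosing rule should not depend on readers setting aside the words of the definition.

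Three stronger readings are tempting and unsupported.

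- **That every ECMO patient is affected.** The parenthesis may confine the loose clause to tracheostomised patients.
- **That the trial loses power, to 60% or so.** The lower rows of the power table rest wholly on an assumed r.
- **That ventilator and ECMO days will not be recorded separately**, because section 11 says "the duration of required mechanical respiratory support or ECMO (in days) will be recorded". The case report form is not shown, and the phrase does not exclude separate fields.

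**Conclusion.** The point holds as a wording fault in the primary endpoint that also reaches the dosing rule. As written, sections 5.1 and 11 allow a patient who has left ECMO but is still ventilated to be scored as weaned and taken off the study drug. This applies at least to a tracheostomised patient, and on the narrow reading of the parenthesis to others. Section 3 and the surrounding context indicate that freedom from both supports was meant, so it is probably a drafting slip.

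The size is 3.3 points per re-scored patient in an arm of 30. The number of such patients is unknown and likely small. A reader might infer a bias towards T3; the documents do not support that, because allocation is blinded and re-scoring could occur in either arm. The 84% power is correct for the planned rates and is not affected.

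**What to change.** Use one sentence in sections 3, 5.1 and 11: successful weaning means free of both ventilatory support and ECMO for 48 consecutive hours, counted from the later of ECMO removal and extubation (or ventilator disconnection if tracheostomised). In section 9, tie the drug stop, under both Maximum duration of treatment and Dosage and Safety, to that definition by cross-reference.

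The cost is one common sentence in three places and a cross-reference in two. Some ECMO patients would receive a longer infusion, within the existing 30-day maximum, and slightly fewer may count as successes. Sample size and test are unchanged.
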